## Abstract

**Background:**

Latent autoimmune diabetes in adults (LADA) is a heterogeneous form of diabetes, characterized by autoimmune destruction of pancreatic β-cells as well as insulin resistance and is triggered by environmental factors in the context of genetic susceptibility. Berberine (BBR), a small alkaloid isolated from medicinal plants, has antidiabetic, anti-inflammatory, and antibacterial effects. Inulin is a common prebiotic that has been shown to improve glycemic control, alter the gut microbiota and suppress inflammation. The primary purpose of this study was to evaluate the effects of oral BBR and inulin combined with insulin therapy on diabetes care in patients with LADA.

**Methods and Analysis:**

We will conduct a single-center, prospective, randomized, double-blind, placebo-controlled trial. A total of 240 patients with LADA who have started insulin therapy will be randomly allocated either to the intervention or control group. After a 1-week run-in period, they will complete a 3-month treatment of BBR alone, inulin plus BBR, inulin alone, or placebo. Anthropometric and clinical data will be collected at five time points: baseline, 3 months, 6 months, 9 months, and 12 months from baseline. The primary outcome was the change in glycated hemoglobin levels. Dynamic blood glucose parameters, β-cell function, and gut microbiota, as well as adverse events and quality of life will be monitored.

**Discussion:**

Glycemic control is critical for preventing the progression of diabetes. Although insulin is a recommended treatment for patients with LADA, there are currently no drugs that can effectively prevent the progressive destruction of pancreatic β-cells or maintain their function. Several studies have found that when berberine and prebiotics are used alone, they have beneficial metabolic effects. This clinical research protocol will assess the efficacy of the combined treatment of berberine plus inulin and provide new ideas for future pharmacological research and clinical practices in diabetes care and glycemic control for LADA patients.

**Ethics and Dissemination:**

This study has been approved by the Ethics Committee of National Clinical Research Center of the Second Xiangya Hospital of Central South University (approval number: 2021–046).

**Clinical Trial Registration:**

ClinicalTrials.gov, identifier NCT04698330

## 1 Introduction

Due to the increased aging population and prolonged life expectancy, the global prevalence of chronic diseases and their complications has caused a huge burden on the socioeconomic and medical costs. Latent autoimmune diabetes in adults (LADA) is a chronic disease that shares the common phenotypic, genetic and pathophysiological features of type 1 diabetes (T1D) and type 2 diabetes (T2D) (1). LADA is typically diagnosed using three criteria proposed by the Immunology of Diabetes Society: (a) adult age of onset (>30 years); (b) the presence of any islet cell autoantibodies, and (c) insulin independence for at least 6 months following diagnosis (2). Diabetes prevalence has risen dramatically in recent years worldwide, and LADA may account for 2–12% of all diabetes in adults (3). Epidemiological studies have shown that there are approximately 6 million patients with LADA in China (4), and LADA patients account for one-tenth of the total population with diabetes in some regions, such as Northern Europe (5). Therefore, the drug treatment and blood glucose management of LADA patients are worthy of our attention.

LADA is characterized by the destruction of pancreatic β-cells caused by autoimmunity and insulin resistance (6). Due to differences in genetics and immunity, LADA has a high degree of heterogeneity. When compared to classic T1D, the autoimmune process of LADA appears to be milder and patients with LADA progress more slowly toward β-cell failure and insulin therapy (7, 8). As a result, health education for LADA patients is essential to promoting good blood glucose management and preserving their remaining β-cell function. Good glycemic control is crucial to prevent future complications and improve patients’ quality of life.

However, a portion of LADA cases can often be misdiagnosed as T2D, with misdiagnosis rates ranging from 5% to 10% in various studies (9). Moreover, misdiagnosed LADA cases are usually treated with therapies commonly used in T2D, which might contribute to the progression of diabetes toward insulin dependence and threaten the health and life of patients (10). Since LADA individuals generally have some residual β-cell function, LADA treatment should aim to achieve good metabolic control while also retaining residual insulin secretion capacity (11). Currently, insulin is the most commonly used therapeutic option for LADA patients. Several randomized clinical trials have found that regardless of the initial C-peptide level and residual β-cell function, clinicians tend to prescribe insulin treatment for LADA patients at an early stage (12). However, whether insulin is truly appropriate as the initial treatment for LADA patients is still debatable. Although LADA patients have better metabolic parameters at baseline than T1D and T2D patients (13), evidence suggests that there is almost no difference in the prognosis of complications and risk of death among the three groups (14–16). Given that insulin alone may not be sufficient to control blood glycemic levels, combination therapy may have the potential to improve long-term blood glucose control and delay disease progression in LADA patients. Because there have been few clinical studies on LADA, more large-scale clinical trials are needed to explore the optimal treatment of LADA.

BBR, an alkaloid compound extracted from many commonly used medicinal plants, such as Coptis chinensis and Berberis asiatica, has been shown in some basic and clinical research to play an important role in alleviating metabolic disorders, improving insulin resistance, regulating intestinal flora, inhibiting inflammation and attenuating intestinal mucosal barrier dysfunction (17–20). A recent study by Jun Yin et al. enrolled 36 adults with new-onset T2D and randomly assigned them to either the BBR or metformin treatment groups (21). They found that similar to the hypoglycemic effect of metformin, BBR can significantly reduce hemoglobin A1c (HbA1c), fasting blood glucose (FBG), postprandial blood glucose (PBG) and plasma triglycerides at the end of the three-month treatment period. The same group of researchers conducted another study in which 48 T2D patients with poor glycemic control were treated with berberine, and they found that the supplementary treatment reduced the subjects’ HbA1c and improved their insulin resistance (21). Furthermore, BBR has low gastrointestinal absorption and a high safety profile, with few adverse reactions and the ability to be tolerated by the human body (22). All of these findings demonstrate BBR’s efficacy as a new candidate drug in the treatment of diabetes and other metabolic diseases.

Inulin, a fructooligosaccharide mixture, is a common prebiotic that has been made into a food grade brewed drink powder. Many studies have found that prebiotics have beneficial metabolic effects in diabetes. A randomized controlled clinical trial in Iran in which 52 women with T2D were randomly assigned to receive oligofructose-enriched inulin or placebo for 8 weeks found that oligofructose-enriched inulin improved the patients’ glycemic control and inflammatory status (23). Josephine Ho et al. conducted a clinical study among children aged 8 to 17 with T1D who received placebo or oligofructose-enriched inulin for 12 weeks (24) and found that C-peptide levels were significantly higher in the prebiotic treatment group, which was accompanied by a moderate improvement in intestinal permeability.

In animal experiments, it has been shown that compared with BBR alone, BBR combined with prebiotics has been shown to continuously reduce FBG, improve glucose tolerance, and ameliorate the balance of α- and β-cells in diabetic db/db mice (25). Similarly, Cao et al. found that the combination of BBR and prebiotics in the intervention of KKAy mice was more effective than BBR alone in blood sugar control, improvement of insulin resistance and pancreatic β-cell function, reduction of inflammatory mediators, and maintenance of intestinal barrier integrity (26). These findings suggest that the combination of BBR and prebiotics may be a novel pharmaceutical strategy for diabetes. Hence, the present study aims to evaluate the effectiveness of combining BBR and inulin on diabetes care, particularly glycemic control in patients with LADA. We will also evaluate the safety and tolerability of the combined drugs.

## 2 Methods

### 2.1 Trial Design

This is a prospective, randomized, double-blinded, placebo-controlled trial with a 1-month washout period, a 1-week run-in period, a 3-month treatment period, and a 9-month follow-up period. The participants will be arranged to enter a 1-month washout period after obtaining their informed consent during which basic treatment medications are adjusted, and then they will be allocated to enter a 1-week run-in period for lifestyle education and collection of baseline data and samples. After the run-in period, they will be randomized 1:1:1:1 to one of four groups: BBR-alone, inulin plus BBR, inulin-alone, or placebo. This study will use a stratified random method to balance the following factors: BMI ≥25 kg/m^2^ and <25 kg/m^2^, with or without chronic complications of diabetes. Measurements will be implemented at baseline prior to the intervention and at 3 months, 6 months, 9 months and 12 months from baseline. The research flowchart is shown in **Figure 1**.

**Figure 1 f1:**
[figure not shown]
Trial flowchart.

#### 2.1.1 Participants

The target population of the trial will be LADA patients between the ages of 30 and 70. Participants will be recruited at a large tertiary first-class hospital in Hunan, China. The following inclusion criteria will be used in the recruitment:

Participants of both sexes aged 30 to 70 with a BMI between 18.5 and 37.5 kg/m^2^; with diabetes diagnosed according to the diagnostic criteria of the World Health Organization (WHO) in 1999; positive glutamic acid decarboxylase antibody (GADA) and HbA1c level ≥ 7.0% and ≤ 10.0%; being insulin-independent for more than 6 months after diagnosis; diabetes duration less than 5 years; fasting serum C-peptide (FCP) level ≥0.15 nmol/L, or 2-hour postprandial C-peptide (2hCP) level ≥0.3 nmol/L; and providing written informed consent will be included.

Participants will be excluded from the trial if they (1) have severe liver dysfunction (ALT and AST levels greater than three times the upper limit of detection); (2) have an eGFR < 50 ml/min/1.73 m^2^; (3) have evidence of acute or chronic infection affecting glycemic control within 4 weeks prior to the first visit; (4) have a history of any malignancy; (5) are pregnant/breastfeeding women; (6) have secondary diabetes; (7) have acute complications (ketoacidosis, lactic acidosis or hyperosmolar coma); (8) have severe organic heart disease, including but not limited to congenital heart disease, rheumatic heart disease, hypertrophic or dilated cardiomyopathy, etc., New York Heart Association (NYHA) heart function classification ≥Grade III; (9) have used corticosteroids or immunosuppressants for over 3 months, or other medications that can cause gastrointestinal reactions 2 months before recruitment and throughout the whole study period; (10) have a history of hemolytic anemia or glucose-6-phosphate dehydrogenase deficiency; and (11) are allergic to berberine hydrochloride or any components in the combinations.

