#### 2.4.3 Data Collection

After the screening, all qualified participants with LADA will enter a 1-month washout period. After the stable control of diabetes with insulin, all enrolled participants will complete the baseline survey for a period of 1 week. The primary endpoint results will be collected after 3 months of intervention. Then, participants will receive outpatient visits every 3 months until the end of the study. The research assistants involved in data collection and evaluation will not be informed of the grouping of participants. The evaluation and data collection process is shown in **Table 1**. The participants will record their daily dose of medications, abnormal self-monitoring of blood glucose levels, combined medications and adverse events. Before each visit, participants will be asked to fill out an online survey of nutritional status in the past week to assess calorie intake, including the content of carbohydrates, fat, protein and fiber in the diet. Nurses will instruct patients to record the type and quantity of daily food *via* online and mobile platforms. In addition, it is worth noting that participants should not consume fermented dairy products (such as yogurt) or probiotics 7 days before the visit and should avoid high-fat diets 3 days before the visit.

**Table 1 T1:** Patient flow of enrolment, intervention and outcome measurements.

		PS	M0	M3	M6	M9	M12
**Enrolment**	Recruitment	×					
	Eligibility Screening	×					
	Informed consent	×					
	Allocation		×				
**Intervention**	Insulin injection	•					•
	Experimental drugs / placebo		•	•			
**Outcomes**	Demographic characteristics (Age, sex, nationality, occupation, marital status, residence and education level)		×				
	Anthropometric variables (BMI, waist and hip circumference, heart rate and blood pressure)	•					•
	Insulin logs		•				•
	Dietary logs		•				•
	CGMS*		•				•
	Metabolic parameters (HbA1C, FBG, PBG, FCP, 2hCP, Triglyceride, Total cholesterol, HDL cholesterol, LDL cholesterol)	•					•
	HOMA-IR**		•				•
	Insulin autoantibody (GADA, IA2A, ZnT8)	×	×	×			×
	Serum inflammation markers		×	×			
	Chronic complication screening (Carotid ultrasound, UCG, fundus examination, urinary albumin-creatinine ratio, eGFR)		×				×
	Gut microbiota (Metagenomics, stool metabolomics, plasma metabolomics)		×	×			×
	Intestinal permeability		×	×			×
	Drug safety assessment (Blood routine, Liver and kidney function testing, Serum electrolytes, Blood ketones, electrocardiogram)		×	×			

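### Exclusion (1) ties the only liver limit for entry to an assay's detection limit where the upper limit of normal is almost certainly meant: a low-severity wording correction

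*Protocol article*

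**What the plan says.** Section 2.1.1 lists eleven exclusions. The first removes patients who "have severe liver dysfunction (ALT and AST levels greater than three times the upper limit of detection"). The second, on kidney function, removes those who "have an eGFR < 50 ml/min/1.73 m^2".

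The liver appears in one other place. Table 1 in section 2.4.3 has the row "Drug safety assessment (Blood routine, Liver and kidney function testing, Serum electrolytes, Blood ketones, electrocardiogram"), marked at M0 and M3, with no numeric limit. M0 is also the column in which allocation is marked.

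On aims, section 1 states: "We will also evaluate the safety and tolerability of the combined drugs".

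**The concern.** Enzyme cut-offs of the form k times a limit work only if the limit marks the boundary between normal and abnormal results. The upper limit of detection marks something else: the highest value the assay can report. It depends on the instrument and carries no information about the patient's liver. Tripling it does not produce a definition of severe dysfunction.

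This is an entry safety threshold, in a trial that gives oral berberine to two of its four arms for 3 months and sets out to evaluate safety and tolerability. Someone who follows the printed number cannot use it to decide whether a patient is eligible. Someone who reads the article later cannot tell from the text which enzyme limit defined the enrolled population. What is at stake is the clarity of one eligibility rule. The efficacy inference is not touched.

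**Working it through.** The article reports no figure that could be reproduced on this point, so the check compares texts.

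**Step 1. What the criterion needs and what it has.**

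| Place | Quantity | Reference for the limit | Usable at the bedside? |
|---|---|---|---|
| 2.1.1, exclusion (1) | ALT and AST | 3 × the assay's upper detection limit | No |
| 2.1.1, exclusion (2) | eGFR | 50 ml/min/1.73 m² | Yes |
| 2.4.3, Table 1, drug-safety row | Liver function tests at M0 and M3 | None given | No limit to apply |

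The kidney criterion beside it shows that the list is meant to hold working cut-offs. The liver criterion has the same form but the wrong reference.

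**Step 2. Does anything correct it?** The liver is named in two places, and one of the two carries a number: exclusion (1) itself. Section 2.4.2 mentions blood biochemistry in general terms, without ALT, AST or a limit. No section gives a reference range or an upper limit of normal for either enzyme. The word normal is not used as a laboratory reference anywhere; in section 2.5 it refers to the distribution of data.

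**Step 3. What the literal rule does.** Let U > 0 be the assay's upper detection limit. A directly reported result x satisfies x ≤ U, and U < 3U, so x > 3U cannot occur. Results from diluted samples could exceed U, but the cut-off would still be set by the analyser. This follows from the definition alone. It shows that the printed reference cannot be the intended one, and it estimates nothing about this trial.

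**Step 4. Does any other number in the plan depend on it?** The sample size in section 2.1.2 uses an HbA1c difference of 0.44, an SD of 0.80, two-sided α = 0.05 and 80% power:

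n = 2 × (1.960 + 0.842)² × 0.80² / 0.44² ≈ 51.9, or 52 per arm,

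against the stated 53, at which power is 0.808. No enzyme value enters. The ANOVA of HbA1c in section 2.5 does not use one either.

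**Step 5. How many patients?** That would need the distribution of ALT and AST among candidates, the laboratory's reference limit and the assay range. The article gives none of them, so no count or range can be stated.

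**The case against.** The strongest reply is that this is one wrong word with an obvious meaning. The criterion opens by naming severe liver dysfunction, and the enzyme limit only explains that phrase in brackets. A clinician at the single tertiary hospital where patients are recruited would exclude such a patient anyway and would read the limit as three times the upper limit of normal. Liver tests are scheduled at M0 and M3 in any case. Section 1 describes berberine as having a high safety profile, and the article names no liver risk for either product. The article also condenses a fuller protocol, which may carry the right term and from which staff would screen.

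Most of this stands, and it limits the weight of the point. It does not remove the error. The article does not leave the limit to another document; it prints a specific number with the wrong reference, and eligibility text should not rely on readers to replace its words silently.

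A reader might go further and infer that the trial has no effective liver exclusion, or that patients with severe liver disease will be enrolled. The documents do not support that. The phrase governing the criterion still calls for exclusion, and nothing shows that screening followed the literal wording. Nor is there evidence that anyone chose this threshold deliberately, so it should not be presented as a design flaw.

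**Conclusion.** The point holds as a low-severity wording correction to an entry safety threshold. As printed, exclusion (1) uses an assay property that cannot define severe liver dysfunction, and the article neither corrects it nor offers another liver limit. The effect is confined to how clearly eligibility is stated; its size in patients cannot be derived.

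The conclusion rests on the article's text alone and on the ordinary meaning of an upper limit of detection. That the upper limit of normal was intended is an inference, though a very probable one: it is the natural reference for such a multiple and the only reading under which the criterion does its job.

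**What to change.** In section 2.1.1, exclusion (1), replace the upper limit of detection with the laboratory's upper limit of normal and keep the multiple of three. If the full protocol and screening forms carry the same wording, correct them in the same way. The cost is one line of text; no test, visit, patient or analysis is added.

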#### 2.1.2 Sample Size Determination

Sample size was determined using published data from a 12-week clinical trial with BBR and probiotics, in which the drugs decreased HbA1c by 0.44% in people with T2D (Zhang, Gu et al., 2020), assuming a common within-group standard deviation (SD) of 0.80% and a two-sided α level of 0.05. With these assumptions, a sample size of 53 evaluable subjects per arm provided 80% power to detect a difference from placebo. Considering the reasonable attrition during the study, we planned to enroll 60 patients per group (i.e., a total of 240 patients).

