### 2.2 Randomization

Once the participants are enrolled, they will be allocated a unique identification number according to their screening order. Participants will be distributed into four treatment groups in a 1:1:1:1 ratio through computerized randomization. A web administrator will independently enter the randomization list, containing consecutive drug numbers, into a blinded datasheet. The numbers will be randomly allocated to participants of the intervention groups or the control group with an opaque, sealed envelope by a third person unaware of the assignments to study groups.

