### 2.5 Data Analysis

Data analysis will be performed using SPSS 26.0 software (IBM, New York, USA). P<0.05 was regarded as statistically significant unless otherwise specified. Descriptive statistics included the mean ± standard deviation for normal distributions, median and interquartile range for otherwise, and frequency and percentage for categorical variables. Intention-to-treat analysis (ITT) will be used and multiple imputations will be handled to manage missing data. Baseline descriptive data between the control group and the intervention groups will be compared using the chi-square test for categorical variables, and ANOVA for continuous variables. The primary outcome of HbA1c will be expressed as the mean HbA1c values with standard deviations, and ANOVA will be used to compare HbA1c between groups. According to the data distribution characteristics, ANOVA or Wilcoxon rank sum test will be used to compare the changes in secondary variables within and between groups. If the difference is significant, pairwise comparisons will be performed with adjustment for multiple comparisons, and ANCOVA will be used with confounding factors such as sex and age as covariates. Spearman’s correlation analysis and partial Spearman’s correlation analysis adjusted for sex and age will be used to evaluate the relationship between changes in intestinal microbial abundance and other markers.

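### The stated 80% power belongs to one unadjusted two-arm test, whereas the written analysis is a four-group ANOVA followed by multiplicity-adjusted pairwise comparisons with no primary contrast named

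*Protocol article*

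**What the plan says.** Section 2.1.2 takes its effect from an earlier trial of berberine with probiotics, in which "the drugs decreased HbA1c by 0.44% in people with T2D". It continues "assuming a common within-group standard deviation (SD) of 0.80" percent and "a two-sided α level of 0.05", and concludes that "a sample size of 53 evaluable subjects per arm provided 80% power to detect a difference from placebo". Enrolment is raised to 60 per arm for attrition. No adjustment for several comparisons enters this calculation.

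Section 2.2 confirms the design: "Participants will be distributed into four treatment groups in a 1:1:1:1 ratio through computerized randomization".

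Section 2.5 gives the primary analysis: "ANOVA will be used to compare HbA1c between groups". A sentence on secondary variables follows, and then: "If the difference is significant, pairwise comparisons will be performed with adjustment for multiple comparisons". No adjustment method is named, and no contrast is singled out for testing at the full 0.05.

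**The concern.** The sizing calculation and the analysis describe different tests. The first is a single comparison of one arm with placebo at an unadjusted 0.05. The second reaches a comparison with placebo only after a 3-df omnibus test has succeeded, and then at a stricter threshold. Four arms give three comparisons with placebo, or six pairs in all.

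The trial's aim is to evaluate the combination. If the written procedure is followed for HbA1c, the chance of missing a true 0.44 effect of the combination at 53 evaluable is not the 20% that readers are told. It is about 32-45% under single-step adjustments.

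**Working it through.** **Inputs.** Section 2.1.2: difference 0.44, SD 0.80, two-sided α 0.05, 53 evaluable per arm, 60 enrolled. Section 2.2: four equal arms. Assumptions, because the article does not give them: the adjustment method and the true means of the other two active arms.

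**1. The plan's own figure.** The normal approximation is n = 2(1.960 + 0.842)² × (0.80/0.44)² = 51.9, so 52 per arm. The exact t-test gives 79.3% at n = 52 and 80.1% at n = 53. The stated 53 is therefore correct for one two-arm, two-sided, unadjusted t-test.

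**2. Adjusted comparison of one arm with placebo, 53 per arm.** SE = 0.80 × √(2/53) = 0.1554, and the noncentrality is 0.44/0.1554 = 2.831. Power is the probability that a noncentral t with pooled 4 × 52 = 208 df exceeds the critical value c. For Bonferroni x3, as a rough check, Φ(2.831 − 2.413) = Φ(0.418) = 66%. The last column requires a significant ANOVA as well. It was simulated (300,000 runs) over five sets of means, all with the combination 0.44 below placebo.

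| Method | c | Power | Power with a significant ANOVA required |
|---|---|---|---|
| Unadjusted | 1.971 | 80% | 63-79% |
| Dunnett | 2.365 | 68% | 61-68% |
| Bonferroni x3 | 2.413 | 66% | 60-66% |
| Tukey | 2.590 | 60% | 57-60% |
| Bonferroni x6 | 2.664 | 57% | 55.5-57% |

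With two-arm df (104), Bonferroni gives 65.5% (x3) and 55.8% (x6). Holm over the three placebo comparisons gives 66-69% when one or two arms work or effects are graded. If all three arms are at 0.44, it gives 74%, or 72% with the ANOVA required. Holm over six pairs gives 57-62%.

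**3. All 60 per arm evaluable.** SE = 0.80 × √(2/60) = 0.1461, and the noncentrality is 3.012. Before any ANOVA requirement, power is 74% (Dunnett), 73% (Bonferroni x3; 72% with two-arm df), 66% (Tukey) and 64% (Bonferroni x6; 63% with two-arm df). Holm over three comparisons reaches at most about 80% (79% with the ANOVA required), and only if all three arms work.

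**4. Omnibus F alone, 53 per arm.** The noncentrality is λ = n × Σ(μᵢ − μ̄)² / SD², with 3 and 208 df.

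| Reductions below placebo (placebo, two single agents, combination) | λ | Power |
|---|---|---|
| 0, 0.22, 0.22, 0.44 | 53 × 0.0968/0.64 = 8.0 | 65% |
| 0, 0, 0, 0.44 | 53 × 0.1452/0.64 = 12.0 | 83% |
| 0, 0.44, 0.44, 0.44 | 12.0 | 83% |
| 0, 0.44, 0, 0.44 | 53 × 0.1936/0.64 = 16.0 | 93% |

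**5. What 80% would take.** Evaluable per arm, before any ANOVA requirement: 70 (Bonferroni x3), 78 (Tukey) or 81 (Bonferroni x6). Alternatively, at 53 per arm the difference detectable with 80% power is about 0.51 (Bonferroni x3) or 0.55 (Bonferroni x6).

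**The case against.** - **The arithmetic is right.** A reader might infer that the sample size was miscalculated. It was not: 53 reproduces exactly. The fault is that the calculation does not match the analysis.
- **The method is unnamed, and a fuller plan may name it.** This stands in part. The 55-68% range is conditional on a single-step method and on 53 evaluable, so it should not be quoted as the trial's power without those conditions. Still, none of the adjustments tried at 53 per arm reaches 80%. A plan that tested one contrast at the full 0.05 would replace the procedure in section 2.5, not fill it in.
- **The pairwise sentence may cover secondary variables only.** It follows the sentence about them, so this cannot be excluded. The adjusted figures would then not apply to HbA1c, and the omnibus F would be the only stated primary test. A reader might go further and infer that the trial will never test an arm against placebo on HbA1c. A condensed article does not support that.
- **Omnibus power can exceed 80%.** It does for several patterns (83-93%). The 65% comes from one assumed pattern, and the article gives no component effects from which to choose. But a significant F does not establish the difference from placebo that section 2.1.2 claims to power.
- **Success could mean at least one arm beating placebo.** On that reading, Bonferroni x3 at 53 per arm gives 88% if all three arms are at 0.44, 82% if two are, 69% for the 0.22, 0.22, 0.44 pattern and 68% if only one works. So it would be too strong to say that the trial falls below 80% on every definition. The sizing inputs, however, describe one arm against placebo, and for that comparison the shortfall remains.

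**Conclusion.** The point holds as a mismatch between section 2.1.2 and section 2.5. The 80% describes a test that the stated analysis does not contain.

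If the adjustment applies to HbA1c, power for a given arm against placebo at a true 0.44 and 53 evaluable is about 55-68% for Bonferroni, Tukey or Dunnett, with or without the omnibus step. It is at most about 72-74% for Holm over three comparisons, when all three arms work. With all 60 evaluable it is about 63-74% for single-step methods before the omnibus step, and at most about 80% for Holm.

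If the adjustment does not apply, the primary test is an F with power of about 65-93%, depending on means that the article does not state. It leaves open which arm differs from placebo.

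All these figures take the plan's 0.44 and 0.80 as given.

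**What to change.** Name one primary contrast for HbA1c change from baseline to month 3. Berberine plus inulin against placebo fits the stated aim, and the sizing effect also comes from a combination trial. Test it at two-sided 0.05 without requiring a significant ANOVA first. The stated 80% at 53 evaluable then holds with no added patients. Treat the remaining comparisons as secondary, under a multiplicity procedure of the sponsor's choice fixed before unblinding. The order or weighting of those comparisons is a trade-off for the sponsor, and this point does not require a particular sequence.

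The cost is a change of wording, plus one real concession: the single-agent comparisons no longer share primary status.

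If the sponsor wants all comparisons on an equal footing, the alternative is to name the adjustment, say explicitly that it covers HbA1c, and restate either the power for that procedure or the difference detectable at 80% power (about 0.51 for Bonferroni x3, 0.55 for Bonferroni x6).
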